## Abstract

**Background:**

Older adults is characterized by an age-related decline in bone mineral density. Frailty-a distinct age-associated geriatric syndrome-further exacerbates this condition. The concomitance of osteoporosis and frailty in older adults markedly heightens the risk of functional decline, with attendant profound psychosocial sequelae. A mixed-methods study design is essential to achieve a comprehensive, patient-centered understanding of this phenomenon.

**Methods:**

This study will adopt a convergent mixed-methods design comprising three primary phases: (1) Quantitative phase: a cross-sectional survey will be conducted among older adults diagnosed with osteoporosis. Data collection will include demographic variables, scores from the Edmonton Frail Scale, Activities of Daily Living assessments, Nutritional Risk Screening assessments, and the Hospital Anxiety and Depression Scale. In addition, handgrip strength will be measured, alongside relevant laboratory parameters. Data will undergo descriptive analysis, followed by univariate analyses and multivariate binary logistic regression to identify factors associated with frailty. (2) Qualitative phase: semi-structured, face-to-face interviews will be performed with participants classified as frail according to their frailty assessment scores, enabling an in-depth exploration of their subjective perceptions and experiences of frailty within the context of osteoporosis. (3) Integration phase: key findings from both quantitative and qualitative components will be analyzed and synthesized to generate a comprehensive understanding of the phenomenon.

**Discussion:**

This study aims to explore the prevalence and clinical characteristics of frailty among older adults with osteoporosis. It also seeks to identify associated risk factors and to explore patients' subjective experiences of living with frailty in the context of osteoporosis.

**Clinical trial registration:**

This trial has been registered with the Chinese Clinical Trial Registry (ChiCTR2500097059).

## Introduction

Osteoporosis (OP) is a systemic skeletal disorder characterized by reduced bone mineral density and microarchitectural deterioration of bone tissue (1). It is highly prevalent among older adults and, owing to its insidious onset and the potentially devastating consequences of fragility fractures, is a major global public health concern. This condition substantially compromises functional independence, contributing to overall functional decline in the aging population (2). A meta-analysis published in 2021 estimated the global prevalence of osteoporosis among older adults at 21.7%, with a higher prevalence of 24.3% reported in older Asian populations (3). Osteoporosis markedly increases the risk of fragility fractures. According to the IOF, one-third of women and one-fifth of men aged ≥50 years will experience a fracture. These events lead to reduced quality of life, higher hospitalization rates, long-term disability, and increased mortality (4, 5). In China, the growing burden of osteoporosis and related fractures is being exacerbated by the rapidly aging population. Recent meta-analyses show a clear age-related increase in prevalence, with rates escalating significantly after age 60 (6). Furthermore, the functional consequences of fractures are severe: approximately 20–30% of patients fail to regain their pre-fracture functional status, experiencing increased dependency and a significantly increased risk of mortality (7).

Frailty is an age-associated geriatric syndrome that represents a critical intermediate state in the aging trajectory. Its defining feature is a decline in physiological reserve, resulting in markedly reduced resilience to both endogenous and exogenous stressors (8). This decline is underpinned by measurable biological processes across multiple domains. Consensus biomarkers for frailty highlight systemic involvement, specifically encompassing the physiological domain (e.g., insulin-like growth factor 1), the inflammatory domain (e.g., high sensitivity C-reactive protein, interleukin-6), and the epigenetic domain (e.g., DNA methylation/epigenetic clocks) (9). Furthermore, frailty extends beyond these physiological deficits to a multidimensional syndrome that severely compromises functional independence (as measured by muscle mass and handgrip strength) and encompasses psychosocial domains, including social support and psychological well-being (10). The clinical significance of this complex syndrome is evidenced by its high prevalence, with epidemiological studies reporting rates reaching 29.8% in hospital settings, and pre-frailty observed in an additional 39.3% of patients (11).

A meta-analysis published in 2025 reported that the prevalence of osteoporosis concomitant with frailty among older adults reached 37.8%. This comorbidity results in physical functional impairment and often precipitates profound psychosocial consequences, including fear of falling, reduced mobility, diminished social participation, symptoms of depression and anxiety, altered self-perception, increased dependency, contributing to an overall psychosocial burden and functional decline (12). This indicates that over one-third of older adults with osteoporosis are also frail, underscoring the urgent need for integrated management approaches. Furthermore, evidence is accumulating to clarify the intricate mechanistic link between these two geriatric syndromes. A recent study utilizing the National Health and Nutrition Examination Survey (NHANES) for a cross-sectional analysis and Mendelian randomization (MR) not only confirmed a significant positive correlation but also established a bidirectional causal relationship between osteoporosis and frailty. Building on this, a prospective study provided crucial mechanistic clarity, demonstrating that chronic low-grade systemic inflammation (indicated by biomarkers like the Neutrophil-to-Lymphocyte Ratio and Systemic Immune-Inflammation Index) acts as an upstream driver. Critically, the frailty phenotype itself partially mediates the association between this systemic inflammation and the resulting increase in osteoporosis and fracture risks (13). These interconnected factors, driven by common pathways including sarcopenia and endocrine dysregulation, collectively amplify the susceptibility to falls and fractures, thereby constituting a significant functional risk for older adults with osteoporosis (14). Although the coexistence of frailty and osteoporosis has been studied epidemiologically, few studies have explored the subjective lived experiences in this population using a mixed-methods design.

This study offers a unique contribution by being among the first to utilize a convergent mixed-methods design for an in-depth exploration of the frailty experience in older adults with osteoporosis within the Chinese context. Most frailty-related research to date has predominantly focused on community-dwelling older adults and patients with chronic conditions such as cardiovascular disease, chronic kidney disease, diabetes mellitus, and cancer (15–17). Research on frailty among patients with osteoporosis remains limited, primarily addressing risk factors and often restricted to a single physiological domain. Notably, there is a paucity of in-depth qualitative investigation into how patients with osteoporosis perceive and understand frailty—specifically, their lived illness experience. Illness experience encompasses patients' perceptions, interpretations, emotional responses, disruptions to daily life trajectories, coping mechanisms, and interactions with healthcare services. Although standardized assessment instruments provide valuable quantitative data, they frequently fail to capture the richness, complexity, and individual variability inherent in the illness experience. Consequently, these tools are insufficient to elucidate the underlying socio-cultural, psychological, and environmental determinants reflected in the scores (18).

Therefore, there is an urgent need for a comprehensive study to characterize the current disease status of older adults with osteoporosis and to explore their lived illness experience in depth. Such research will provide an essential foundation for the development of more precise and patient-centered intervention strategies. To address this research gap, the present study will employ a concurrent convergent mixed-methods design. This methodology facilitates a holistic understanding of frailty in older adults with osteoporosis through a threefold integrative approach that combines quantitative and qualitative data (19). Ultimately, by integrating these two perspectives, this study moves beyond the quantification of risk factors to explore the subjective lived experiences of frailty—a crucial step for developing holistic, patient-centered interventions.

This study aims to: (1) determine the prevalence and current status of frailty among older adults with osteoporosis; (2) identify factors associated with frailty within this population; (3) explore the subjective illness experiences of frailty in older adults with osteoporosis; (4) analyse potential discrepancies between healthcare system frailty management recommendations and patients' illness perceptions; and (5) elucidate conflicting mechanisms between qualitative and quantitative findings through triangulation analysis. By addressing these objectives, this research seeks to provide evidence-based insights to inform the development of precise, patient-centered nursing care and health policy.

## Materials and methods

### Study design

This study will employ a convergent mixed-methods approach, involving the concurrent collection of quantitative and qualitative data within the orthopedic wards of a tertiary hospital from February to December 2025. Data will be analyzed separately before integrating the results (see Figure 1).

**Figure 1 F1:**
[figure not shown]
Flowchart of the convergent mixed-methods study design.

The study will proceed through three sequential yet interrelated phases:

(1) Quantitative phase

A cross-sectional survey will be administered to older adults diagnosed with osteoporosis.Data will include: demographic characteristics; Edmonton Frail Scale (EFS) scores; Activities of Daily Living (ADL) assessments; Nutritional Risk Screening (NRS) scores; Hospital Anxiety and Depression Scale (HADS) scores; handgrip strength measurements; and relevant laboratory parameters.Statistical analysis will involve descriptive statistics, univariate analyses, and multivariate binary logistic regression to identify factors associated with frailty.

(2) Qualitative phase

Semi-structured, face-to-face interviews will be conducted with patients classified as frail based on their frailty scores.This component aims to provide an in-depth exploration of participants' lived experiences of frailty in the context of osteoporosis.

(3) Integration phase

Principal findings from both datasets will be compared and synthesized.Integration will be achieved through joint display analysis and narrative synthesis, enabling the identification of convergent, complementary, or divergent findings.his phase is designed to yield novel insights and enhance clinical practice guidance for frailty management in osteoporotic patients.

### Ethics and registration

This study received ethical approval from the Medical Ethics Committee of Peking University Shenzhen Hospital, Beijing, China (approval number [2025] No. 003). It has also been registered with the Chinese Clinical Trial Registry (registration number ChiCTR2500097059). Prior to participation, all subjects will be fully informed of the study's purpose and significance and will provide written informed consent, in accordance with the Declaration of Helsinki.

### Stage1: quantitative study

For the quantitative component, this cross-sectional study will employ convenience sampling to recruit patients diagnosed with osteoporosis from a tertiary A-level hospital in Shenzhen, Guangdong Province, China. However, we acknowledge that convenience sampling may introduce selection bias, which could limit the representativeness of the sample and the generalizability of the findings.

#### Participants

Inclusion criteria are:

(1) Age ≥ 65 years;(2) Osteoporosis Diagnosis: diagnosis of osteoporosis based on any of the following:

a dual-energy *X*-ray absorptiometry (DXA) *T*-score of ≤ −2.5 at the axial skeleton or distal one-third radius;a history of fragility fracture of the hip or vertebra;osteopenia (−2.5 < *T*-score < −1.0) accompanied by a fragility fracture of the proximal humerus, pelvis, or distal forearm (20);

(3) Possessing good communication skills, the ability to read questionnaires effectively, and intact cognitive function (e.g., scoring ≥24 on the Mini-Mental State Examination [MMSE] threshold);(4) voluntary participation with signed informed consent.

Exclusion criteria are:

(1) Patients with other critical or unstable illnesses, such as active malignant tumors or severe, acute cardiorespiratory insufficiency;(2) Patients exhibiting severe disability, bedridden status, or conditions that severely limit mobility required for frailty assessments;(3) A history of stroke or severe head trauma, or existing central nervous system diseases;(4) Individuals unable to cooperate with questionnaire surveys or frailty assessments.

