#### Instrument

Data will be collected using the following research instruments:

The General Information Questionnaire will collect 17 variables: sex, age, height, weight, body mass index (BMI), marital status, living arrangements, educational attainment, monthly household income, medical expense reimbursement method, presence of insomnia, exercise habits, smoking status, alcohol consumption, calcium supplementation, history of falls within the previous 6 months, and 17 comorbid conditions.Edmonton Frail Scale (EFS): developed by Rolfson et al. in 2006, the Edmonton Frail Scale (EFS) provides a comprehensive assessment of frailty encompassing physical, psychological, and social domains (22). This 11-item instrument evaluates frailty across nine key domains: cognition, general health status, independence, social support, medication use, nutrition, mood, continence, and self-reported functional performance. Cognitive function is assessed using the Clock Drawing Test, while mobility is measured via the Timed Up and Go (TUG) test. Independence in activities of daily living is quantified by the number of independently completed tasks out of eight routine activities, including cooking, cleaning, and shopping. The EFS yields a total score ranging from 0 to 17, with higher scores indicating greater frailty severity. The scale is user-friendly, practical, and can be administered within approximately 10 min, making it suitable for rapid frailty screening by both healthcare professionals and trained non-professionals. Internal consistency is acceptable, with a reported Cronbach's alpha coefficient of 0.62.Activities of Daily Living Assessment Scale (ADL): the Barthel Index is a widely used instrument to evaluate activities of daily living in older adult patients. This scale comprises 10 items, including feeding, grooming, dressing, bowel control, bladder control, toilet use, transfers (bed to chair), ambulation on level surfaces, and stair climbing (23). The total score ranges from 0 to 100, with higher scores indicating greater independence in performing daily self-care tasks. Based on the total score, patients' functional status is classified into five categories: complete dependence (0–20 points), severe dependence (21–40 points), moderate dependence (41–60 points), mild dependence (61–99 points), and complete independence (100 points).Nutritional Risk Screening Assessment Scale: the Nutritional Risk Screening 2002 (NRS-2002) was developed through international collaboration among researchers from Denmark, the United Kingdom, France, and other countries. It is designed to evaluate changes in nutritional status based on parameters such as weight variation over the preceding 3 months and dietary intake during the past week (24). The scale demonstrates moderate reliability, with a Kappa coefficient (κ) of 0.67, a sensitivity of 0.86, and a specificity of 0.37.Hospital Anxiety and Depression Scale (HADS): developed by Zigmond et al. in 1983, the Hospital Anxiety and Depression Scale (HADS) is a self-administered instrument designed to evaluate anxiety and depression symptoms experienced by patients over the preceding week (25). It comprises two subscales—anxiety and depression—each containing seven items scored on a four-point Likert scale ranging from 0 to 3. The total score for each subscale ranges from 0 to 21. Scores are interpreted as follows: 0–7 denotes no clinically significant symptoms; 8–10 indicates possible presence of anxiety or depressive symptoms; and 11–21 reflects probable clinical anxiety or depression. The internal consistency reliability, expressed by Cronbach's α coefficients, is 0.879 for the total scale, and 0.806 for both the anxiety and depression subscales.Muscle Strength Assessment: muscle strength will be evaluated using a handheld dynamometer. Participants will be instructed to perform a maximal voluntary isometric contraction by gripping the dynamometer handle with their dominant hand for 2–3 s. Two measurements will be recorded, with the highest value (expressed in kilograms) retained as the final result, reported to two decimal places.Laboratory Indicators: within 24 h of admission, the following laboratory parameters will be collected: neutrophil percentage (%), hemoglobin (g/L), C-reactive protein (mg/L), serum calcium (mmol/L), and serum creatinine (μmol/L). Normal reference ranges are as follows: neutrophil percentage: 40–75%. Hemoglobin: 130–175 g/L for males, 115–150 g/L for females. C-reactive protein: 0–10 mg/L. Serum calcium: 2.11–2.52 mmol/L. Serum creatinine: 57–111 μmol/L for males, 41–81 μmol/L for females.

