
#### Date collection

Under the supervision of the research team, standardized training on study procedures will be provided. After explaining the study's purpose and significance and obtaining informed consent, data will be collected via one-to-one interviews. For inpatients, questionnaires will be administered following their daily treatments and once they report no significant discomfort. If participants are unable to complete the questionnaire independently, the investigator will record responses based on participants' verbal reports.

Demographic data, Edmonton Frail Scale (EFS) scores, Activities of Daily Living (ADL) assessments, Nutritional Risk Screening (NRS) assessments, Hospital Anxiety and Depression Scale (HADS) scores, and muscle strength measurements will be collected through face-to-face interviews. Laboratory parameters will be retrieved from the electronic medical records system. Each questionnaire is estimated to require 15–20 min for completion. All questionnaires will be administered and collected on-site.

Following the survey, investigators will offer psychological support to participants to mitigate any distress experienced during questionnaire completion. Throughout the study, the ethical principles of autonomy, confidentiality, and non-maleficence will be rigorously upheld. Finally, all assessment results will be independently reviewed by two qualified medical professionals with a minimum of intermediate-level clinical credentials to reduce potential bias.

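### Eligibility selects on components of the frailty scale, so the prevalence estimate does not describe the older adults with osteoporosis named in objective 1, and the stated limitations do not mention this

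*Protocol article*

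**What the plan says.** The aims paragraph at the end of the Introduction sets objective 1 as to "determine the prevalence and current status of frailty among older adults with osteoporosis". The Discussion carries the expected results to the same broad group, including support for routine frailty screening across all of them.

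The Stage 1 Participants section is narrower. It requires "Possessing good communication skills, the ability to read questionnaires effectively, and intact cognitive function", with an MMSE score of at least 24 as the example threshold. It excludes "Patients exhibiting severe disability, bedridden status, or conditions that severely limit mobility required for frailty assessments", then "A history of stroke or severe head trauma, or existing central nervous system diseases", then "Individuals unable to cooperate with questionnaire surveys or frailty assessments".

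The Instrument section describes the outcome scale: "Cognitive function is assessed using the Clock Drawing Test, while mobility is measured via the Timed Up and Go (TUG) test". Independence is scored as the number of eight routine activities completed unaided.

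On administration, the data collection section of Stage 1 says: "If participants are unable to complete the questionnaire independently, the investigator will record responses" from what participants say.

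Two limitations bear on representativeness. The opening of Stage 1 acknowledges selection bias from convenience sampling, and the Discussion acknowledges a single recruitment site.

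**The concern.** Cognition, mobility and independence contribute to the frailty score, and the criteria remove people at the poor end of each. This is more specific than ordinary limited generalisability. Among the ward patients from whom the sample is drawn, it has an expected direction: the people removed are likely to be frail more often than those kept. A random multicentre sample under the same criteria would share the problem, so the two acknowledged limitations do not cover it.

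At stake is the meaning of the main descriptive result. As written, the study would attach its prevalence to a population it did not sample. The same truncation could attenuate some of the associations sought under objective 2. For example, the Instrument section lists Barthel categories for severe and complete dependence, which eligibility will leave largely empty.

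The reading requirement raises a smaller, related issue. It can exclude low-literacy patients although verbal answers may be recorded. Educational attainment is both a collected variable and a purposive sampling factor for the interviews.

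**Working it through.** **Step 1. The plan's own precision figure.** Inputs from the Stage 1 Sample size section: P = 0.533, Z = 1.96, d = 0.1 × P = 0.0533.

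n = Z² P(1 − P)/d² = 1.96² × 0.533 × 0.467 / 0.0533² = 336.6, so 337. The plan states 343, which is within 2%. At n = 343 the half-width is 1.96 × √(0.533 × 0.467/343) = 0.0528. The planned margin of about 5.3 points is therefore a fair yardstick.

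**Step 2. Overlap between eligibility and outcome.**

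| Scored on the frailty scale | Matching eligibility criterion |
|---|---|
| Cognition (clock drawing) | Intact cognition required; stroke and CNS disease excluded |
| Mobility (Timed Up and Go) | Severely limited mobility and bedridden status excluded |
| Independence in eight activities | Severe disability excluded |

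General health, social support, medication, nutrition, mood and continence are also scored, and eligibility does not select on them directly.

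**Step 3. Size of the bias.** Let f be the share of ward patients with osteoporosis excluded on these grounds, q the frailty prevalence among them, and p the prevalence among the eligible. Neither f nor q is in the documents; both are assumptions here. Prevalence in the whole group is (1 − f)p + fq, so the estimate falls short by f(q − p). With p = 0.533, the shortfall in percentage points is:

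| q | f = 5% | 10% | 15% | 20% | 30% | f needed to pass 5.33 points |
|---|---|---|---|---|---|---|
| 60% | 0.3 | 0.7 | 1.0 | 1.3 | 2.0 | 79.6% |
| 70% | 0.8 | 1.7 | 2.5 | 3.3 | 5.0 | 31.9% |
| 80% | 1.3 | 2.7 | 4.0 | 5.3 | 8.0 | 20.0% |
| 90% | 1.8 | 3.7 | 5.5 | 7.3 | 11.0 | 14.5% |
| 100% | 2.3 | 4.7 | 7.0 | 9.3 | 14.0 | 11.4% |

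The last column is 0.0533/(q − 0.533); for q = 0.9 this is 0.0533/0.367 = 0.145.

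**Step 4. Sensitivity to the starting prevalence.** If 53.3% is instead the prevalence in the whole group, the shortfall is f(q − 0.533)/(1 − f). The thresholds become 10.2% (q = 100%), 12.7% (90%), 16.6% (80%), 24.2% (70%) and 44.3% (60%). If the Introduction's other figure, 37.8%, is the prevalence among the eligible, they are 0.0533/0.622 = 8.6% (q = 100%), 0.0533/0.522 = 10.2% (90%) and 0.0533/0.422 = 12.6% (80%).

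**Step 5. Direction against the population in objective 1.** Recruitment is from the orthopaedic wards of one tertiary hospital, and a hip or vertebral fragility fracture is by itself a qualifying diagnosis. Relative to all older adults with osteoporosis, this may raise prevalence. The two selections can oppose each other, and the documents give no figure for either.

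**The case against.** A reader might infer that the estimate is biased low by more than its margin of error. The documents do not support that. Both driving quantities are unknown. With 10% excluded and every one of them frail, the shortfall is 0.1 × 0.467 = 4.7 points, still inside the margin. A very high frailty rate is also hard to defend for everyone excluded: nothing in the documents suggests it for patients who cannot read or who have any history of stroke. Against the wider population, even the direction is open, as step 5 shows. This part of the objection stands.

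A reader might also infer that the frailest patients cannot enter at all, or that every association is weakened. Neither is shown. The mobility and disability exclusions are limited to severe cases. Slow but ambulant patients, partly dependent patients, and those who meet the MMSE threshold but fail the clock drawing can all be enrolled. In a binary logistic model, selection that depends only on the binary outcome does not by itself bias odds ratios. Loss of the severe end may attenuate some associations, but no more can be said. Nor is a shortage shown for the 15–20 interviews.

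Three further points are fair. Patients who cannot perform the tests or answer questions are reasonably left out. The article does give a general caution on representativeness. A screening log may sit in the full protocol, so its absence here is no fault. None of this removes the mismatch: the objective and conclusions still name a wider group, and the caution does not mention eligibility.

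On reading, the Instrument section describes the anxiety and depression scale as self-administered, and verbal recording is a fallback. The two provisions can be reconciled; simply deleting the requirement is not compelled.

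**Conclusion.** The point holds as a mismatch between target and sample. The criteria select on components of the outcome scale, objective 1 and the Discussion refer to older adults with osteoporosis in general, and the limitations do not name the mechanism.

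Among orthopaedic ward patients the criteria tend to lower the estimate, provided the excluded are frail more often than the included. The amount is conditional. With 53.3% among the eligible, it exceeds 5.33 points only above about 11%, 14.5% or 20% excluded, for excluded frailty rates of 100%, 90% and 80%; otherwise it is smaller. Such shares are conceivable on these wards but not documented. No net direction can be claimed for all older adults with osteoporosis. The point deserves correction because it affects what the first objective can conclude, and the correction is cheap.

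**What to change.** 1. Restate objective 1 and the prevalence conclusions as applying to assessable, cognitively intact orthopaedic inpatients with osteoporosis. Add to the limitations that eligibility selects on components of the frailty scale.

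2. Tally otherwise eligible patients excluded for disability, mobility or cognition, by reason, with age and sex. Beside the main estimate, report an upper-bound prevalence that counts them as frail: (1 − f)p + f, with f taken from the tally. For illustration, at p = 53.3% this is 0.9 × 53.3% + 10% = 58.0% with 10% excluded, and 0.8 × 53.3% + 20% = 62.6% with 20% excluded. The bound applies to ward patients, not to all older adults with osteoporosis.

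3. Reconcile the requirement for "the ability to read questionnaires effectively, and intact cognitive function" with the verbal administration already permitted, so that patients with low literacy who can answer aloud are not excluded without need.

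The cost is some rewording, a short tally sheet and one extra reported line. The downside is a narrower stated target population.
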